### Objectives

The objective of this protocol paper is to provide a detailed description of the Preschool Plates cohort study methods. Preschool Plates is a population-based, longitudinal cohort study that was designed to improve upon the rigor of prior studies to advance our understanding of the use and impact of food parenting practices in important ways. Specifically, the Preschool Plates cohort study aims to: (1) describe within- and between-day fluctuations in food parenting practices across time and context, (2) examine the longitudinal impact of within- and between-day fluctuations in food parenting practices on child dietary intake, and (3) identify momentary predictors of within- and between-day fluctuations in food parenting practices across time and context.

Findings from Preschool Plates will deepen our understanding of how clinicians and public health practitioners can best support parents in adopting and maintaining the use of supportive food parenting practices despite momentary day-to-day challenges.

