### Statistical Analysis Plan

#### Overview

R (R Foundation for Statistical Computing) will be used for data cleaning and main analyses. Distributions of key outcome variables will be assessed and transformed if necessary. Unless otherwise specified, hypothesis tests will be conducted using a 2-sided α level of .05.

EMA responses will be aggregated to derive scores for each of the 4 food parenting practice domains during each data collection period. Given the unequal number of questions related to each domain, 2 versions of domain scores will be created by computing (1) the number of items endorsed in each domain and (2) the proportion of items endorsed in each domain. Domain scores will be calculated for responses given at each event prompt (typically 2-8 per day over each 8-day data collection period).

Food parenting practice domain scores will be aggregated and compared visually and statistically at the event level (eg, breakfast, lunch, snack, and dinner) and by time period (eg, 9 AM to noon, 3 PM-5 PM, and 5 PM-9 PM). In addition, for each data collection period, we will fit linear mixed models for each domain of the form (M1) *D_ij_ = β_0_ + β_1_Z_ij_ + β_2_X_i_ + b_i_ + ε_ij_*, where *D_ij_* is the domain score for person *i* at event prompt *j*, *Z_ij_* is the event characteristic of interest (meal or time period indicator), *X_i_* is a set of baseline characteristics for person *i*, *b_i_* is a person-specific random effect, and *ε_ij_* is the residual. Longitudinal response patterns in domain scores will be visualized and qualitatively compared. We will calculate each individual’s SD, IQR, and entropy of domain scores across their longitudinal observations. How between-day fluctuations in food parenting differ across individuals will be quantified using longitudinal mixed models, similar to those described above, with the event characteristics *Z_ij_* representing between-day factors such as day of the week. The SD, IQR, and entropy of residuals from these models will also be summarized to characterize between-day fluctuations.

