To examine the longitudinal impact of within- and between-day fluctuations in food parenting practices on child dietary intake, we will fit regression models for the outcome of child HEI measured from 24-hour dietary recall at time points T2 to T4. The main predictors of interest will be the individual-level summary measures of the 4 food parenting practice domains derived above. Our primary models will include the subgroup indicators classifying parents according to food parenting practice patterns, but we will also consider models that use average domain scores as well as consistency and endurance metrics. We will fit separate linear regressions for each data collection period, as well as longitudinal models that incorporate data across the time points T2 to T4. For period-specific models, we will include cluster indicators as well as consistency *z* scores that reflect the degree of within- and between-day fluctuations in food parenting practices during that period, along with relevant adjustment covariates. For longitudinal models, we will also include endurance *z* scores that reflect whether food parenting practices are maintained across data collection periods.

To identify momentary predictors of within- and- between-day fluctuations in the use of food parenting practices across time and context, we will combine the signal and event EMA survey data to understand how momentary factors (eg, mood, stress, and time constraints) affect food parenting practices. The main statistical approach will be to fit longitudinal linear mixed models of the form: (M2) *D_ij_* = *β_0_* + *β_1_W_ij_* + *β_2_X_i_* + *b_i_* + *ε_ij_*. Here, *W_ij_* represents a *vector* of momentary predictors, which will be derived by summarizing signal surveys within fixed time windows before the event *j*. Initially, we will define 

, with the superscript in parentheses indicating the number of hours before the event covered by that variable. For instance, 

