 could reflect the average level of stress reported from signal surveys responded to in the 3 hours preceding the given event survey. We will fit separate models for each domain score during each data collection period; to increase power, we will also fit combined models that incorporate responses across multiple data collection periods. Single-predictor models (involving 1 type of momentary predictor, eg, stress) as well as multipredictor models will be considered. Time windows will be adjusted based on the observed response patterns of data, and if the momentary predictor data are overly sparse, multiple imputation will be used to fill in missing *W*values. In exploratory analyses, we will investigate whether momentary predictors interact with each other or with fixed and summarized individual characteristics (ie, consistency and endurance *z* scores) to impact food parenting practices. This will allow us to explore whether the strength of associations between momentary predictors and food parenting practices varies based on individuals’ levels of volatility in these practices.

Some participants may respond sporadically to event prompts, resulting in gaps between event prompt responses, which make it difficult to assess longitudinal patterns. We will begin by characterizing missing data patterns by participant and temporal factors, including the end-of-day prompts asking participants to indicate why they did not respond to prompts on a given day. Then, we will define and analyze a subset of “regularly responding” individuals for which there is sufficient data to characterize between-day fluctuations in food parenting practices, for example, a subset of individuals who have at most 2 days of event prompt nonresponse during their data collection period. To explore overall patterns and associations with non-EMA outcomes, we will augment this regularly responding set with data from individuals with more sporadic response patterns but who, based on their responses to end-of-day prompts, more plausibly have responses missing at random (eg, reported “forgot” rather than “too stressed”).

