## Results

### Overview

Recruitment and data collection began in October 2023. At the time of this protocol paper’s submission, data collection is still in progress and is expected to continue through November 2026. A racially and ethnically diverse cohort was successfully enrolled, with 28.3% (72/254) of enrolled participants identifying as White and 71.7% (182/254) identifying as Black, Indigenous, or people of color. Refer to Table 2 for detailed information on the characteristics of the Preschool Plates baseline sample.

Hypotheses

This study hypothesized the following:

Use of food parenting practices will vary within- and between-days; unique patterns will emerge across time (eg, time of day and day of week) and context (eg, location and type of eating occasion).Distinct patterns in food parenting approaches will emerge; distinct pattern features will include mean levels of engagement in specific food parenting practices (by domain), as well as consistency in approach across day-, week-, and 6-month intervals, and endurance (or lack thereof) of patterns across time.Healthful eating occasion–level dietary quality (ie, Healthfulness of Meal Index assessed via EMA) will be positively associated with supportive feeding practices (eg, structure and autonomy support) and inversely associated with unsupportive practices (eg, coercive control and indulgent).Consistent and enduring use of supportive feeding practices will be associated with a more healthful overall diet quality (ie, HEI assessed via 24-hour dietary recalls) cross-sectionally and at 2-year follow-up, as compared to inconsistent or short-lived use of supportive practices and consistent and enduring use of unsupportive practices.We expect to identify numerous momentary predictors of significance (eg, mood, stress, child behavior, and time constraints). Parents will shift within the day from supportive feeding practices toward unsupportive feeding practices in response to momentary predictors (eg, high stress, low mood, or limited time).

**Table 2 table2:** Characteristics of the Preschool Plates baseline sample (N=254).

Characteristics		Values
Child age (y), mean (SD)		3.48 (0.59)

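### Model M2 gives each momentary predictor one slope that blends between-parent, between-day and within-day associations, so it cannot by itself support the within-day shift in hypothesis 5

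*Protocol article*

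**What the plan says.** The Objectives set aim 3 as to "identify momentary predictors of within- and between-day fluctuations in food parenting practices across time and context", which names two levels of variation. Hypothesis 5 (Results, Hypotheses) is narrower: "Parents will shift within the day from supportive feeding practices toward unsupportive feeding practices in response to momentary predictors".

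The model for this aim is in the Statistical Analysis Plan, Overview: "The main statistical approach will be to fit longitudinal linear mixed models of the form" M2, D_ij = β0 + β1·W_ij + β2·X_i + b_i + ε_ij. The term b_i "is a person-specific random effect" (defined under M1; the same symbol is used in M2). W_ij is a vector "of momentary predictors, which will be derived by summarizing signal surveys within fixed time windows before the event". The one worked example is a variable that "could reflect the average level of stress reported from signal surveys responded to in the 3 hours preceding the given event survey".

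The readable text contains no parent-mean term, day-mean term, day-level random effect or statement of centring. The displayed formula for W did not survive in the text available here. What remains shows only that its elements carry a superscript for the hours covered.

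**The concern.** A stress score taken before a meal can be high for three reasons: this parent is usually stressed, this is a bad day, or this is a bad moment within an ordinary day. Only the third bears on a shift within the day. M2 assigns all three to one coefficient per predictor. The person intercept does not remove the first, because the model takes b_i to be unrelated to W. Nothing in the model addresses the second.

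The test of β1 at the plan's general level ("hypothesis tests will be conducted using a 2-sided α level of .05") could therefore be significant when no within-day shift exists. The Conclusions look ahead to a real-time intervention triggered by momentary circumstances. A between-family or bad-day association would not show that such a trigger acts at the right moment.

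**Working it through.** **1. Inputs from the article.** Power Analysis: 200 families, at least 32 observations each, 6400 data points per domain; detectable differences at 80% power of 0.14 items (momentary predictor) and 0.55 items (between-person covariate). Ecological Momentary Assessment: a complete day needs 2 event and 2 signal responses. Domain scores come from event prompts, so the floor is 2 × 8 = 16 events per parent.

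**2. The article's own figures.** The 0.14 and 0.55 come from a simulation whose variances are not given, so they cannot be reproduced independently. They can be back-solved, taking a 50/50 binary covariate and detectable difference = (1.960 + 0.842) × SE:
- Within: SE² = 4σ²w/6400, so σ²w = (0.14/2.802)² × 6400/4 ≈ 4.00.
- Between: SE² = 4(σ²b + σ²w/32)/200, so σ²b = (0.55/2.802)² × 200/4 − 4.00/32 ≈ 1.80.
- Intraclass correlation = 1.80/5.80 = 0.31.

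The two figures are mutually coherent.

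**3. Weights in the M2 slope.** Let W have variance shares p (parent), d (day) and o (occasion), with D = 8 days, m events a day and n = Dm. Put λ = σ²w/(σ²w + nσ²b). The generalised-least-squares slope weights the three level-specific slopes in proportion to
- parent: nλp
- day: m(D − 1 + λ)d
- occasion: (n − 1 + λ)o

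λ = 4/(4 + 32 × 1.8) = 0.065 for n = 32, and 4/(4 + 16 × 1.8) = 0.122 for n = 16. The shares are assumptions.

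| p / d / o | n = 32: parent, day, occasion | n = 16: parent, day, occasion |
|---|---|---|
| 0.3 / 0.2 / 0.5 | 3%, 26%, 71% | 5%, 26%, 69% |
| 0.5 / 0.15 / 0.35 | 6%, 26%, 67% | 12%, 25%, 63% |
| 0.4 / 0.3 / 0.3 | 4%, 46%, 50% | 8%, 45%, 47% |
| 0.7 / 0.1 / 0.2 | 14%, 27%, 59% | 24%, 24%, 52% |

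Example (third row, n = 32): 0.83, 8.48 and 9.32, total 18.63, so day = 8.48/18.63 = 46%.

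**4. Consequence when the true within-day slope is zero.** Simulation of 200 parents, 200 replicates, first three share sets, W scaled to unit variance. A pure day-level slope of 0.3 items gives:

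| p / d / o | 4 events a day: mean M2 slope, significant | 2 events a day: mean M2 slope, significant |
|---|---|---|
| 0.3 / 0.2 / 0.5 | 0.076, 74% | 0.080, 46% |
| 0.5 / 0.15 / 0.35 | 0.077, 59% | 0.076, 35% |
| 0.4 / 0.3 / 0.3 | 0.134, 96% | 0.131, 83% |

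The slopes agree with 0.3 × day weight (0.078, 0.079 and 0.137 at n = 32). A pure parent-level slope of 0.55 gives M2 slopes of only 0.02-0.03 and significance in 9-11% of runs with 32 observations, and 8-22% with 16. A slope on deviations from the parent's own day mean averages about zero and rejects in about 5% of runs (range 3-10%).

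**5. Equal slopes.** With a slope of 0.2 at all three levels, M2 and the day-centred slope both recover about 0.20. The bias exists only when the levels differ.

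**6. Price of separation.** The standard error rises from 0.030, 0.035 and 0.033 to 0.041, 0.049 and 0.053 with 4 events a day (ratios 1.37, 1.40, 1.61). It rises from 0.043, 0.049 and 0.046 to 0.071, 0.084 and 0.091 with 2 (ratios 1.65, 1.71, 1.98). With 4 a day, 0.14 × 1.37 = 0.19 and 0.14 × 1.61 = 0.23 items.

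**The case against.** The strongest reply is that the definition of W is not visible. W is a vector indexed by hours, multipredictor models are planned, and windows are to be adjusted to the data. If several windows enter together, a longer one could partly stand in for the day level. Centring is also something a fuller analysis plan could hold. This limits the point to the model as printed. It does not remove it: the equation is written term by term, the surviving example is a plain average, and overlapping windows would not isolate a contrast within the day.

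A second reply is that between-day prediction belongs to aim 3, so capturing it is no error. That stands. The fault is only that it shares a coefficient with the within-day effect.

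A third reply concerns families. A reader might infer that stable differences between stressed and unstressed parents are what M2 would report as a within-day shift. The documents do not support that. Mental health, income and employment are all collected and may enter X_i, although its contents are not listed. With a parent-level correlation of 0.3 left after adjustment, the spurious slope is about 0.01-0.04 SD per SD of W at 16 to 32 events. Rejection is then about 15-50% at 16 events and 10-32% at 32. With a correlation of 0.15 it falls to 6-15% and 7-13%.

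A reader might also extend the criticism to hypothesis 3, on meal-level diet quality. The article writes out no model for that hypothesis, so there is nothing to correct there.

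**Conclusion.** The point holds for M2 as printed. A significant coefficient would not by itself establish hypothesis 5 or tell within-day from between-day predictors. The main contamination is between-day, at roughly a quarter to nearly half of the slope's weight; the between-parent share is a minority that grows as usable events become fewer. These sizes rest on assumed variance shares for W, on variances back-solved from the article's detectable differences, and on W being uncentred.

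It would go too far to say that M2 results will be spurious: the occasion level carries 47-71% of the weight in the settings shown, and equal slopes leave no bias. The study is observational, has no formally defined primary end point, and loses no data through this. The rating is therefore should-fix.

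**What to change.** In M2, replace each predictor by three terms: the parent's mean in that collection period; the day mean minus the parent's mean; and the value minus the day mean. Add a day-within-parent random intercept. Judge hypothesis 5 on the third term, report the second as the between-day predictor, and report the first as a between-family association only.

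Where most days yield a single W value, which is possible when a complete day needs only 2 signal responses, use the two-part split (parent mean and deviation) and call the result a within-parent effect, not a within-day one. State in the plan how W is defined and whether it is centred.

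The change needs a recode and analysis-plan wording, with no new data. The real cost is precision. The 0.14-item detectable difference should be restated for the within-day term: roughly 0.19-0.23 items with 4 usable events a day under the assumptions above, and larger with 2.

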#### Ecological Momentary Assessment

EMAs were used to assess specific food parenting practices used during shared eating occasions, as well as to identify momentary predictors of within- and between-day variability in use of specific food parenting practices.

The EMA protocol included 2 distinct types of assessments. the first was event-contingent assessments; for these, caregivers were asked to complete an EMA survey after every eating occasion during which they were present with the enrolled child. Event-contingent assessments were initiated by caregivers after each shared eating occasion (eg, meals or snacks); caregivers simply used their phone to click on a study-provided link. Event-contingent assessments included questions on food parenting practices and the child’s food intake during that specific eating occasion. On average, participants took 4.41 (SD 6.35) minutes and a median of 2.77 minutes (IQR 1.90-4.32) to complete each event prompt. The second was signal-contingent assessments, for which caregivers were texted to complete a survey at random intervals situated within 4 time blocks throughout the day (eg, 7 AM-10 AM) to capture momentary variables of interest. Signal-contingent prompts were timed to expire after 1 hour of receipt of the text prompt. On average, participants took 1.74 (SD 2.71) minutes and a median of 1.22 (IQR 0.85-1.82) minutes to complete each signal prompt.

Caregivers were asked to complete 8 days of EMA data collection. A day was considered to be complete if they engaged in 2 event-contingent and 2 signal-contingent assessments; if a parent failed to complete adequate prompts on a specific day, they were given an additional day to complete the required prompts. At baseline, on average, it took parents 9.667 (SD 3.63 days; median 9.0, IQR 8-10) days to achieve 8 complete days. To minimize potential confounding effects of weekly rhythms (eg, weekday vs weekend variations in behavior, mood, or context), all participants began data collection on the same day of the week. This approach, which followed recommendations in the extant EMA literature [47-50], ensures that each participant’s data collection period spanned identical calendar days.

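### Model M2, the main Aim 3 model, has no time-of-day term, so any daily rhythm shared by momentary predictors and feeding practices would enter the momentary coefficient

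*Protocol article*

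**What the plan says.** All model text is in the protocol article, Statistical Analysis Plan, Overview.

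- **M1** describes how domain scores vary. Its event-level term Z_ij "is the event characteristic of interest (meal or time period indicator"), and X_i "is a set of baseline characteristics for person" i. A between-day version lets Z_ij stand for factors such as day of the week.
- **M2** serves Aim 3: "The main statistical approach will be to fit longitudinal linear mixed models of the form" D_ij = β0 + β1·W_ij + β2·X_i + b_i + ε_ij. W_ij is a vector of momentary predictors, "which will be derived by summarizing signal surveys within fixed time windows before the event". As an example, one element "could reflect the average level of stress reported from signal surveys responded to in the 3 hours preceding the given event survey".
- **Variants of M2** that are named: single- and multi-predictor versions, adjusted windows, multiple imputation of sparse W, models pooled over collection periods, and interactions with other momentary predictors, individual characteristics or subgroups. None is a meal-type or time-of-day term.
- **Hypothesis 1** expects that "unique patterns will emerge across time (eg, time of day and day of week) and context". **Hypothesis 5** expects parents to move within the day towards unsupportive practices when stress is high, mood is low or time is short.
- **Ecological Momentary Assessment** section: signals fall in four blocks of the day. Weekly rhythms ("weekday vs weekend variations in behavior, mood, or context") are recognised and handled by a common start day. Time of day is not mentioned as a source of confounding.

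**The concern.** M1 exists because the study expects practices to differ by occasion and hour. M2 has the same outcome, but W_ij takes the place of Z_ij. What remains besides W_ij, namely X_i and b_i, does not change within a parent and can only adjust for differences between parents.

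Each W_ij comes from a window just before the event, so it belongs to a particular part of the day. If stress or time pressure tends to run higher before evening events, and practices also differ in the evening for other reasons, M2 will show an association even when stress has no effect. Centring W on each parent's mean would not help, because the shared rhythm lies within parents. If the two rhythms run in opposite directions, a true effect could be masked.

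The plan means to read this coefficient as a response to the moment. The Overview asks how momentary factors affect practices, and the Conclusions look ahead to a real-time intervention that reacts to context. A coefficient that partly stands for the hour would point to the wrong trigger.

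**Working it through.** **1. The plan's own figure.** The Power Analysis states 80% power for a difference of 0.14 items for momentary predictors, with 200 × 32 = 6400 observations. It comes from a simulation whose inputs are not printed, so it can only be solved backwards. For a binary predictor with prevalence p that varies within parents:

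SE = SD_within / √(6400 × (31/32) × p(1−p)), and 0.14 = (1.960 + 0.842) × SE, so SE = 0.050.

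- p = 0.5: SD_within = 0.050 × √1550 = 1.97 items
- p = 0.3: 1.80 items
- p = 0.2: 0.050 × √992 = 1.57 items

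The plan's 0.55-item figure for between-person covariates then implies an intraclass correlation of about 0.32, so the two figures are compatible.

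**2. Bias by hand, true effect zero (assumed inputs).** Take one period of the day, for example the dinner period, holding 25% of events and having 0.5 more items endorsed. The spurious difference is the period effect × [P(period | high stress) − P(period | low stress)].

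- High stress before 40% of events in that period and 20% of others: P(high) = 0.10 + 0.15 = 0.25; P(period | high) = 0.10/0.25 = 0.40; P(period | low) = 0.15/0.75 = 0.20. Difference = 0.5 × 0.20 = **0.10 items**.
- 50% and 20%: P(high) = 0.125 + 0.15 = 0.275; 0.125/0.275 = 0.455; 0.125/0.725 = 0.172. Difference = 0.5 × 0.282 = **0.141 items**.
- With a 0.3-item period effect: 0.06 and 0.085 items.
- If either rhythm is flat: 0.

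**3. Simulation, true effect zero.** 200 parents × 8 days × 4 time slots; within-parent SD 1.95 (from step 1), random-intercept SD 1.3; 400 runs per setting; within-parent estimator. All rhythm sizes are assumptions. Prevalences are for a parent at the centre of the between-parent distribution.

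| Rise in score, morning to evening | High stress, morning to evening | M2 as printed: mean estimate | Rejection | With time-slot terms: mean estimate | Rejection |
|---|---|---|---|---|---|
| 0 | 20 to 50% | −0.005 | 5.5% | −0.005 | 4.8% |
| 0.5 | flat at 35% | −0.001 | 4.3% | −0.001 | 4.8% |
| 0.25 | 30 to 40% | 0.016 | 3.5% | 0.000 | 3.0% |
| 0.25 | 20 to 50% | 0.052 | 16.0% | 0.005 | 7.3% |
| 0.5 | 30 to 40% | 0.031 | 9.3% | 0.000 | 5.8% |
| 0.5 | 20 to 50% | 0.094 | 40.5% | 0.000 | 5.0% |
| 0.5 | 15 to 60% | 0.142 | 73.3% | −0.002 | 4.8% |
| 1.0 | 20 to 50% | 0.192 | 93.5% | 0.002 | 4.3% |
| 1.0 | 15 to 60% | 0.287 | 100% | 0.001 | 4.8% |

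With 400 runs, a true 5% rejection rate has a simulation standard error of √(0.05 × 0.95/400) = 1.1 percentage points, so the last column is in line with 5%. Five full mixed-model fits at rise 0.5 and 20 to 50% agreed in direction: mean estimate 0.09 without the slot terms and −0.01 with them.

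**The case against.** **The source is condensed.** The article speaks of models of a given form and is brief about covariates elsewhere, so the full analysis plan may contain a time term. Part of the definition of W_ij is also missing from the text at hand, although what survives describes the hours before the event that each variable covers, not a clock term. This calls for caution. It does not dispose of the point: the article prints the whole equation, calls it the main approach and lists its variants, and anyone following it would fit M2 without a time term.

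**The bias is conditional.** A reader might infer that M2 will necessarily report the daily rhythm as a stress effect. The documents do not support that. It needs a rhythm on both sides, and only the one in practices is stated. Weak rhythms leave almost nothing, as the table shows. Rejection rates also depend on the residual SD, and a value below the 1.57 to 1.97 range would inflate them. This objection stands and limits the claim.

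**Meal type is not clearly a confounder.** A reader might infer that the whole of Z_ij belongs in the main M2. W_ij is measured before the event, so the meal cannot cause it; time of day is the plausible common cause. A rushed or stressed parent may offer a snack in place of a meal, and adjusting for meal type could then remove part of the effect being sought. This stands and narrows the remedy.

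**The aims are descriptive.** The Power Analysis says that the goal is to describe patterns and associations, and a future randomised trial would test any trigger. That softens the consequence, but hypothesis 5 still words the result as a response.

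**Conclusion.** The point holds in conditional form. M2 as printed omits a time-of-day term that the same section already defines for M1, and nothing else in M2 can do its work. How far this biases the momentary coefficient depends on two rhythms whose sizes the article does not give.

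Under the assumptions above and no true effect, the spurious difference is about 0 if either rhythm is flat, 0.02 to 0.10 items for weak to moderate shared rhythms, and 0.14 items or more for strong ones. The last of these equals or exceeds the difference that the study says it can detect with 80% power. With a time-of-day term the estimate stayed within ±0.006 items of zero, and rejection was near 5% in every setting. The day-of-week part was not simulated. It rests on the plan's own recognition of weekly rhythms: a common start day makes the calendar comparable across parents but does not remove a weekday-weekend association within a parent.

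**What to change.** Write the main Aim 3 model as D_ij = β0 + β1·W_ij + β2·X_i + β3·T_ij + b_i + ε_ij. Here T_ij holds the time-period indicators already defined for M1 and the day-of-week term from its between-day version. Use this form for the single- and multi-predictor models and for those pooled over collection periods. State that β1 is interpreted within time of day.

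Report two companions: the same model with meal type added, as a sensitivity analysis, with a note that meal type may be a consequence of stress or time pressure; and M2 without T_ij, as a contrast showing how much of the association follows the clock.

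The cost is a few degrees of freedom, slightly less precision and a narrower interpretation. No new data are needed, and with data collection expected to run through November 2026 the wording can be changed before the final analysis.
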